**Myasthenias**

Twelve patients with generalised and refractory myasthenia with anti-RAch antibodies will be included in the study.

If success is observed in at least 6 patients, it will be possible to conclude that the response rate is above 25% (limit lower than 90% of the confidence interval for an observed response rate of 50%).

For a given subject, efficacy is determined by an improvement in muscle strength defined by at least a 20-point gain in the MMG score (47, 48) in the 12th month.

## 7.2. Statistical analyses

Statistical analysis will be carried out after all the data has been verified and will include:

- - description of the patient population
  - description of the efficacy criteria (clinical and biological)
  - description of the tolerance criteria (clinical and biological)
  - description of the immune response

The primary and secondary criteria for evolution in the muscle testing scores, evolution in the quality of life, evolution in the CPKs and in the AAB titer, etc., will be assessed by the individual variation in the measurement compared to the measurement taken at D0.

Statistical tests will be carried out on the individual data using the percentages for qualitative variables and averages (interquartile range) for the quantitative variables.

The statistical analyses will be carried out within the Inserm U 720 unit under the responsibility of [name].

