**Generalised myasthenia**

- An improvement in muscle strength, defined by an increase of at least 20 points in the MMG score (47, 48) at day 21, in month 6 and in M18.

- An improvement in MGFA postintervention status (45).

- An improvement in the ADLs score

- - An improvement in quality of life (SF 36 self-evaluation).

- A reduction in the number of clinical exacerbations that require either hospitalisation or a change in corticosteroid doses.

- A reduction in corticosteroid doses and related treatments

- A decrease in autoantibody levels.

- An increase in vital capacity.

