**Generalised myasthenia**

1. Clinical exam with MMG and MGFA testing (44, 45)
2. Echocardiography

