### Inclusion period: Day – 1(D-1) to day + 2 (D2).

### Myositides and myasthenias

**Day – 1 (D-1)**:

Clinical exam with muscle testing and standard biological exams (CBC, serum electrolytes, full hepatic assessment (gamma GT, alkaline phosphatase, ASAT/ALAT, Bilirubin), CPK, ßhCG for women) specific to ancillary studies, quality of life, vital capacity for myasthenia.

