**M12 (+/-8 days)**:

Clinical exam with neuro-muscular testing and standard biological exams (CBC, serum electrolytes, full hepatic assessment, CPK) specific to ancillary studies.

Neuromuscular assessment: EMG and muscle MRI (Myositis only)

Pulmonary function tests

Quality of life

Recording of intercurrent events and related medications

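### The ADLs score is a secondary criterion for generalised myasthenia, but no visit is scheduled to measure it, so improvement from baseline cannot be assessed under the schedule as it stands

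*Protocol*

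**What the plan says.** Section 3.2 lists "An improvement in the ADLs score" and "An improvement in MGFA postintervention status (45") among the secondary objectives for generalised myasthenia. Section 4.1 repeats both as secondary criteria. Neither section gives a time point for either one.

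Section 7.2 says that the primary and secondary criteria "will be assessed by the individual variation in the measurement compared to the measurement taken at D0". It names muscle testing, quality of life and then "evolution in the CPKs and in the AAB titer, etc". The next sentence provides for statistical work "using the percentages for qualitative variables".

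The assessments at each visit are set out in section 4.3:

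- The pre-inclusion visit for myasthenia starts with "Clinical exam with MMG and MGFA testing (44, 45").
- The D-1 list has muscle testing and biology, and ends with items "specific to ancillary studies, quality of life, vital capacity for myasthenia".
- The M12 list has "Clinical exam with neuro-muscular testing and standard biological exams", then pulmonary function tests and quality of life.

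**The concern.** An improvement needs one value before treatment and one after it. The protocol declares an ADLs objective but asks no site to record the score at any time.

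The study is open and has no control group, so change within the patient is its only evidence of efficacy, and a baseline is essential for any scored outcome. A post-treatment visit that was overlooked can be added by amendment while patients are still in follow-up. A pre-treatment score cannot be added for a patient who has already been infused. If some centres record the score on their own initiative and others do not, the result would describe a self-selected part of a group that has only 12 patients.

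**Working it through.** No formula or published figure is involved. The check is whether each of the eight myasthenia secondary criteria in section 4.1 has a scheduled source before and after the first infusion. The sources are section 4.3, the synopsis procedure, the two schedule tables and section 6.

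| Criterion | Before first infusion | Afterwards |
|---|---|---|
| MMG score | MMG named at pre-inclusion; muscle testing at D-1 | Neuro-muscular testing at D21, M6.5, M12, M18 |
| MGFA postintervention status | MGFA testing named at pre-inclusion | Not named; may fall within neuro-muscular testing |
| ADLs score | None | None |
| SF-36 | D-1 | M12 |
| Exacerbations | Not a baseline measurement | Record of intercurrent events and medications |
| Corticosteroids and related treatments | Medications recorded from D0 | Medications recorded at each visit |
| Autoantibody level | Before the first injection (section 6, toxicity assessment) | Before the later injections |
| Vital capacity | D-1 | M12 (synopsis; pulmonary function tests in 4.3) |

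**ADLs score.** The schedule tables have 10 visit columns and 11 row labels. The marks in the cells cannot be read in the text at hand, but the labels can, and none is for ADLs. The visit lists name it at 0 visits. Quality of life and vital capacity each have their own row and their own mention in the D-1 list, so the protocol's habit is to list such measures separately from the clinical exam and muscle testing. Section 4.1 ties the MMG score and the SF-36 to an appendix, and ties the ADLs score to none. A myasthenia activities-of-daily-living profile stands in the reference list (reference 46), but sections 3.2 and 4.1 do not cite it.

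Under the section 7.2 rule, change = value after treatment − value at D0. For the ADLs score, the schedule requires neither term.

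**MGFA status.** Pre-inclusion is the only visit that names MGFA testing. It precedes treatment, and the protocol does not say whether this testing is a baseline class or the status itself. By its name, a postintervention status has no value at D0, so subtracting a D0 value does not suit it. The sentence on qualitative variables allows percentages instead, which a categorical status fits. What is left open is the visit at which the status is assigned.

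**The case against.** The visit lists are not exhaustive. Autoantibody titration is also a secondary criterion, and section 4.3 does not name it at the visits. The CRF and the appendices are not available, and either could contain an ADLs form. This limits the point: it shows that the protocol does not require the score, not that nobody will collect it. The comparison with autoantibodies does not rescue the ADLs score, because titration is scheduled elsewhere, in the toxicity assessment of section 6. An SAP could not close the gap either, since it can define an analysis but cannot create a baseline assessment that the schedule never asked for.

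A reader might go further and infer that neither the ADLs score nor the MGFA status can be derived, so that two of the eight criteria are lost for all 12 patients. The documents do not support that for the MGFA status, for three reasons:

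- The change-from-D0 sentence names neither criterion and reaches them only through its closing etc. It cannot be literal for every criterion, because a count of exacerbations has no D0 measurement either.
- The following sentence already offers percentages for a qualitative variable, so no analyst has to invent a baseline category.
- The pre-inclusion list describes myasthenia testing as MMG and MGFA together. After that visit the MMG score is not named either; the lists speak only of muscle or neuro-muscular testing. If that wording covers the MMG score, it may equally cover MGFA.

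**Conclusion.** The point holds for the ADLs score. It is a declared secondary objective and criterion with no scheduled assessment before or after treatment, so a trial run to this schedule cannot say whether the score improved. This rests on one assumption: that no CRF page or appendix outside the documents already requires the score at baseline.

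The size is modest. One of eight secondary criteria is affected, in one group of 12 patients, and the analysis of it is descriptive. The primary criterion (change in MMG score at M12) and the rule of at least 6 successes among 12 patients are unaffected. It is still worth correcting, because a lost baseline is irrecoverable and the correction is cheap.

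For the MGFA postintervention status, only a minor clarification is warranted. The visits at which it is assigned are not named, and a change from D0 is the wrong summary for it. It is not shown to be underivable.

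**What to change.** In section 4.3, the synopsis procedure and both schedule tables, add the ADLs score for myasthenia patients at D-1 and at least at M12. Ideally add it also at the other visits with neuro-muscular testing (D21, M6.5 and M18). In sections 3.2 and 4.1, state the time point at which improvement is judged, and cite the instrument.

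For the MGFA postintervention status, name the post-treatment visits at which it is assigned. Say in section 7.2 that it is reported as the percentage of patients in each category at those visits, not as a change from D0.

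The cost is wording in these sections, one CRF page and a few minutes at visits that already take place. No visit or procedure is added, and treatment is not affected. For the ADLs score to be complete, the change has to be in force before the first myasthenia patient is infused. Patients infused earlier without a score would have to be reported as having no baseline.

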# 8. Regulatory aspects:

## 8.1. Anticipated methods and timetable for measuring, collecting and analysing the parameters for assessing safety

## 8.1.1.Steering Committee

The committee will be made up of the clinicians who initiated the project, the biostatistician responsible for the project, representatives of the sponsor and the URC named for this study.

The committee will determine the general organisation and procedure for the study and will coordinate the information.

This includes initial determination of the methodology and during the course of the study, determination of the approach to be adopted in unexpected situations. The committee will also monitor the conduct of the study, in particular relating to tolerance and adverse events.

## 8.1.2. Independent Supervisory Committee

A supervisory committee that is independent of the study will be put in place.

Its composition will be determined at the start of the study. It will be made up of individuals with no connection to the study including at least one clinician specialising in the pathology being studied and a pharmacologist/pharmacovigilance specialist.

This committee consultative and decision-making role in advising the sponsor on medical issues such as tolerance and adverse events.

This supervisory committee will meet in order to assess the side effects seen in the first 4 patients to receive a combination of azathioprine and rituximab after 6 months of treatment, as well as after the first 4 patients to receive a combination of mycophenolate mofetil and rituximab.

The study can be interrupted at any time by decision of the supervisory committee, in particular if serious adverse reactions occur more frequently than expected (see below) after the rituximab injections.

## 8.2. Description of parameters for assessing safety

#### Adverse event

Any untoward medical occurrence in a biomedical research subject, which does not necessarily have a causal relationship with the study or with the product being studied.

#### Adverse reaction to an experimental medication

Any untoward and adverse reaction to an experimental medication regardless of the dose administered

#### Serious adverse event or reaction

Any adverse event or reaction that results in death, threatens the life of the research subject, requires hospitalisation or prolongs hospitalisation, causes a severe or long-term disability or handicap, or results in a congenital abnormality or deformity, and in the case of a medication, regardless of the dose administered.

#### Unexpected adverse reaction to an experimental medication

Any adverse reaction of which the nature, severity or evolution are not consistent with the information provided in the summary of the product characteristics if the medication is authorised, and in the investigator's brochure if the medication is not authorised.

#### New fact

Any new information regarding safety, that could lead to a reassessment of the benefit-risk ratio for the study or experimental medication, or which could be sufficient to consider modifications to the administration of the experimental medication, during the study.

## 8.3. Procedures in place for recording and reporting adverse events

## 8.3.1 Non-serious adverse events

Any adverse event - non serious according to the definition above - observed during the study and during follow-up must be reported in the relevant section of the case report form.

Only one event must be reported per item. The event can be a symptom, a diagnosis or the result of an additional test considered to be significant. All the clinical or para-clinical elements that make it possible to describe the events as accurately possible must be reported.

## 8.3.2 Serious adverse events (SAE):

The investigators must report serious adverse events as defined above to the AP-HP as sponsor **immediately**.

**The investigator completes the serious adverse events forms (in the case report form for the study) and sends them to the DRCD by fax at [name] within 48 hours** (if possible, after making a telephone call immediately to [name] in the case of death or in a life-threatening situation).

The investigator must also inform the URC responsible for the study that the SAE has occurred.

For each serious adverse event, **the investigator must issue an opinion on the causal relationship between the event and each experimental medication and any other treatments.**

Obtaining information about the description and assessment of an adverse event might be impossible in the time given for the initial declaration.

**Therefore, the clinical evolution and the results of any clinical reports and diagnostic and/or laboratory exams, or any other information making it possible to adequately analyse the casual relationship, will be reported:**

- **either on the initial declaration of the SAE if this is available immediately**
- **or subsequently and as soon as possible, by faxing a new completed SAE declaration (and specifying that this is a follow-up to a reported SAE, including the follow-up number).**

All the declarations made by the investigators must identify each subject participating in the study **with a unique code number** assigned to each participant.

**If the death of a participant is reported**, **the investigator will provide the sponsor and the ethics committee with all additional information requested** (hospitalisation report, autopsy report, etc.).

Any new facts that occur during the study or in the context of the study, originating from data in the literature or from ongoing studies, must be reported to the sponsor.

#### *- Declaring serious adverse events to the Health Authorities*

This is carried out by the Pharmacovigilance Division of the DRCD, after an assessment of the severity of the adverse event, the causal relationship with each experimental medication and any other treatments and the unexpected nature of the adverse events.

The promoter must report all suspected unexpected serious adverse reactions to the competent authorities within the legal time frame.

**The promoter will report any safety data or new fact that could significantly alter the assessment of the benefit-risk ratio for the experimental medication, or for the study, or which could lead to the possibility of altering the administration of the experimental medication or altering the conduct of the study, to the competent authorities, to the Comité de Protection des Personnes (ethical review board) and to the study investigators.** For example:

a) any clinically significant increase in the frequency with which an expected serious adverse reaction appears

b) suspected unexpected serious adverse reactions occurring in patients who have finished the trial and about whom the sponsor is notified by the investigator, who also provides any follow-up reports

c) any new fact relating to the conduct of the clinical trial or the development of the medication, if the new fact is likely to affect participant safety Examples:

- a serious adverse event likely to be related to the investigations and to the trial's diagnostic procedures and which could modify the conduct of this trial
- a significant risk for the trial participants such as ineffectiveness of the medication used in the trial in treating a life-threatening illness
- significant safety results from a recently completed study carried out on animals (such as a carcinogenicity study)
- the premature termination, or temporary interruption, of a trial conducted with the same medication in another country, for safety reasons
- an unexpected serious adverse reaction associated with a non-experimental medication required for carrying out the trial, (e.g.: challenge agents, rescue treatment)

d) recommendations from the independent supervisory committee, if applicable, if they are relevant to the safety of the participants

e) any unexpected serious adverse reaction reported to the sponsor by another sponsor of a trial carried out in a different country but relating to the same medication

## 8.4. Procedures for and duration of participant monitoring after adverse events have occurred

All patients presenting an adverse event must be monitored until the event is resolved or stabilises.

- If the event is not serious, its evolution will be reported on the corresponding page of the relevant section on the case report form
- If the event is serious, SAE follow-up will be sent to the DRCD.

# 9 RIGHT TO ACCESS SOURCE DATA AND DOCUMENTS

People with direct access in accordance with the legislative and regulatory provisions in force, and particularly Articles L.1121-3 and R.5121-13 of the Public Health Code (e.g. investigators, quality control officers, monitors, clinical research assistants, auditors and anyone invited to collaborate in the study) will take all necessary precautions to preserve the confidentiality of information about the experimental medications, the trials, the trial participants and in particular the identity of the participants and the results obtained. The data collected by these people during quality inspections and audits will therefore be kept anonymous.

# 10 QUALITY CONTROL AND ASSURANCE

**Research will be supervised according to the sponsor’s standard procedures.**

The conduct of the study in the investigating centres and management of the subjects will be undertaken in accordance with the Declaration of Helsinki and current Good Clinical Practice.

## 10.1 Monitoring procedures

This study is classified as D risk according to the promoter's procedures.

The CRAs representing the sponsor will visit the investigating centres at a rate corresponding to the patient follow-up plan in the protocol, inclusion in the various centres and the risk level attributed to the research.

- Opening visit of each centre: before inclusion, to set up the protocol and make contact with the various biomedical research agents.

- During subsequent visits, the case report forms will be reviewed by the CRAs as research progresses. Each centre’s principal investigator and the other investigators who will include or monitor the subjects undertake to welcome the CRAs at regular intervals.

During these onsite visits and in keeping with Good Clinical Practice, the following points will be reviewed:

- Adherence to the defined research protocol and procedures
- Verification of the patients' informed consent forms
- Examination of source documents and comparison with the data in the case report forms regarding accuracy, missing data and data consistency according to the rules set out in the procedures of the DRCD

- Closing visit: collection of the case report forms, pharmacy report, biomedical research documents, archiving

## 10.2 Transcription of the data in the case report form

All information required under the protocol will need to be entered onto the case report form and the investigator will need to provide an explanation for all missing data.

All clinical and para-clinical data will need to be transferred to the case report forms as they are obtained. Data will need to be copied onto these forms clearly and legibly, using black ink (to facilitate duplication and computer entry).

If incorrect data are found on a case report form, they will be clearly crossed off and new data will be copied onto the form with the date and the initials of the investigating team’s member who makes the correction.

Anonymity will be preserved by using each subject’s code number and initials on all required research documents and by deleting personal data from copies of source documents intended for research documentation using the appropriate means.

Data on computer files will be declared to the French data protection authority using the appropriate procedure.

# 11. LEGAL AND ETHICAL CONSIDERATIONS

The sponsor is defined by French Act 2004-806 of 9 August 2004. In this study, AP-HP is the sponsor and the Département de la Recherche Clinique et du Développement (Clinical Research and Development Department, DRCD) performs regulatory missions.

*Before starting research, each investigator will give the sponsor’s representative a copy of his/her* ***personal curriculum vitæ, dated and signed,*** *with his/her number of registration in the Order of Physicians.*

## 11.1 Request for authorisation from AFSSAPS

To be able to start the study, AP-HP, as sponsor, has to submit a request for authorisation to the competent authority, AFSSAPS. The competent authority, defined in Article L. 1123-12, will give its opinion as to the safety of the study participants, considering particularly the safety and quality of the products used during the study in accordance, where applicable, with the guidelines in force, their conditions of use and personal safety with regard to the acts performed and the methods and procedures used for participant follow-up.

## 11.2 Request for an Opinion from the Comité de Protection des Personnes (ethical review board)

In accordance with Article L.1123-6 of the Public Health Code, the sponsor has to submit the research protocol to an ethical review board. The board’s opinion is notified by the sponsor to the competent authority before the start of research.

